## Blinding

In this trial, outcome assessors, and data analysts will be blinded to the treatment allocation to minimize potential sources of bias and the clinical researcher, assessor, and statistician will not share study information with each other. After the end of the experiment, we will use a questionnaire to ask the participants if they know whether they received real acupuncture or sham acupuncture.

## Intervention

All practitioners in this trial are licensed TCM acupuncture therapists with at least 5 years of clinical experience, and they will be trained to master the study protocol. The acupuncturist will be asked to administer the standard manipulation.

## Treatment Group

The treatment group will receive electroacupuncture and 36-h ASD. The choice of acupuncture points is based on a previous study (18). The acupoints will be Baihui (GV20), Sishencong (EX-HN1), and Shenting (GV24). Acupuncture at these acupoints mentioned above can regulate Qi of Governor Vessel, clear the mind, lift the spirits, nourish Yang based on Chinese acupuncture theory (39). Modern research shows that Baihui, Shenting and sishencong acupuncture can alleviates cognitive impairment (40–42).We will use sterile, disposable stainless-steel needles of the Hwato brand measuring 0.30 × 25 mm, with horizontal needling of 12–20 mm following an angle of 0–15°. After eliciting the Deqi response, the researcher will apply electroacupuncture by connecting an acupoint nerve stimulator (G6805-2A) to Baihui (GV20) and Shenting (GV24). The stimulation parameters are dense wave, frequency of 5 Hz, current of 1–5 mA, and needle retention for 30 min, with intervention performed every 12 h.

## Placebo Group

Placebo group is intervened with sham electroacupuncture. The sham GV20 point is 0.5 cun (≈12.5 mm) lateral to GV20, the sham EX-HN1 point is 0.5 cun (≈12.5 mm) horizontal to EX-HN1 and the sham GV24 point is 0.5 cun (≈12.5 mm) horizontal to GV24, pierce of 3–5 mm following an angle of 0–15°. Procedures, electrode placements, and other treatment settings are the same as in the treatment group but with no electricity output and needle manipulation for de qi.

## Control Group

Participants in the control group will receive only 36-h ASD but will not receive electroacupuncture treatment.

## Blank Group

The healthy control group will not receive any intervention. They will keep normal work and rest time.

## Visual Go/No-Go Task Design

At the beginning of the visual Go/No-Go task, a small white cross (+) on a black background appears at the center of the screen for 100 ms before each trial, followed by the stimulus. Each stimulus is presented for a duration of 100 ms, with an inter-stimulus interval of 800 ms. The task has two blocks with 150 trials in each block. In one block, the subjects are asked to respond to the left arrow [target stimulus (Go)] and withhold responding to the right arrow [non-target stimulus (No-Go)], while in the other block, the response pattern is reversed. The Go stimuli occur with a one-third probability, and the sequence of Go/No-Go stimuli is pseudorandom to ensure that the No-Go stimuli do not appear in a continuous sequence. The participants will undergo a training session to ensure that they understand the Go/No-Go task and that their performance is above 90%.

The participants will arrive at the lab at 20:00 p.m. and perform a Go/No-Go task as a baseline. They will be asked to ensure that they get a full night's sleep (by wearing a wrist-operated sleep monitor and “sleep log” to ensure that they get at least 8 h of sleep), and the experiment will begin at 8:00 a.m. the next morning, taking the Go/No-Go task as 0 h. The participants will not be allowed to sleep for the next 36 h, during which time they will receive acupuncture every 11 h. After 36 h, the participants will be asked to complete the Go/No-Go task again. They will be accompanied and supervised by 10 staff members, and there will be two emergency doctors and nurses in the laboratory at all times. The participants will be asked to stay in the laboratory and will be allowed to talk, read, play computer games, and engage in other non-strenuous activities. They will not be allowed to smoke or drink coffee, tea, hot chocolate, wine, or other bladder-irritating drinks (Figure 1).

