Executive function (also called executive control or cognitive control) is fundamental to human cognition (21). It is a top-down mental process needed when one has to concentrate and pay attention, when going on automatic or relying on instinct would be insufficient (22–24). There are three core executive functions: inhibition, working memory (WM), and cognitive flexibility (25, 26). The Go/No-go paradigm has been used to study the executive function (27). Event-related potential (ERP) has often been used to investigate the effects of sleep deprivation on neurocognitive functioning. It is non-invasive and simple to perform, and it does not entail discomfort for participants. Certain components of ERP have been found to reflect specific forms of information processing related to sensory, motor and/or cognitive functions (28). The visual Go/No-go task is often used to study response inhibition (29). There have been several reports supporting the hypothesis that the visual N2 reflects a frontal inhibition mechanism (30, 31), including cognitive control and response inhibition (32, 33). Furthermore, recent studies suggest that P3 may play an important role in the post-response stage, reflecting processes of cognitive processing, such as stimulus identification and evaluation (34, 35) or monitoring of inhibition (36, 37).

This high-quality randomized controlled trial (RCT) was designed *via* a pragmatic trial approach to objectively assess the efficacy of electroacupuncture for brain cognition using ERP. By comparing ERP related to response inhibition tasks before and after ASD, we can understand the effect of ASD on the brain's inhibition control and the effect of electroacupuncture on brain cognition function after ASD.

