### Objectives

The aim of this study is to assess the effect of electroacupuncture on brain inhibition control function.

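### The Go/No-Go task cannot have Go on one-third of trials and also keep No-Go stimuli from following one another; the ratio and the sequence rule must be reconciled

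*Protocol article*

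**What the plan says.** Under Visual Go/No-Go Task Design, the Protocol article fixes the size of the task ("The task has two blocks with 150 trials in each block"), the share of Go trials and the type of ordering ("The Go stimuli occur with a one-third probability, and the sequence of Go/No-Go stimuli is pseudorandom"), and the purpose of that ordering ("to ensure that the No-Go stimuli do not appear in a continuous sequence"). In one block the left arrow calls for a response and subjects must "withhold responding to the right arrow [non-target stimulus (No-Go)], while in the other block, the response pattern is reversed". The arrows therefore change roles between blocks, while the Go share stays the same.

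The task has a defined purpose. The Objectives section states: "The aim of this study is to assess the effect of electroacupuncture on brain inhibition control function". The Background introduces the paradigm with "The visual Go/No-go task is often used to study response inhibition". Under Secondary Outcomes, false alarms on No-Go trials and the N2 and P3 components are among the measures taken from the task. The article gives no other Go/No-Go ratio and no maximum run length.

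**The concern.** The ratio and the ordering rule appear in the same sentence and conflict. If No-Go is two-thirds of trials, No-Go stimuli must often follow one another. Whoever programs the task has to break one of the two statements, and the article does not say which.

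The choice affects what the task measures. With Go on two-thirds of trials, responding is the dominant tendency and a No-Go trial asks the subject to suppress it. With Go on one-third, withholding is the majority response and the rare stimulus is the one to be answered. Contrasts between Go and No-Go ERPs then mix inhibition with target rarity. Data collected under an unintended ratio cannot be repaired afterwards.

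**Working it through.** **Inputs**, all from Visual Go/No-Go Task Design: 2 blocks, 150 trials per block, Go probability 1/3, No-Go not in a continuous sequence.

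**Trial counts.** Go per block = 150 × 1/3 = 50. No-Go per block = 150 − 50 = 100. Over the two blocks: 100 Go and 200 No-Go.

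**Strict reading: no two No-Go in succession.** With g Go trials there are g + 1 gaps (before, between and after them), and each gap can hold at most one No-Go.
- Per block: 50 + 1 = 51 gaps for 100 No-Go. At least 100 − 51 = 49 No-Go trials must follow another No-Go, and no sequence satisfies the rule.
- Whole task as one sequence: 100 + 1 = 101 gaps for 200 No-Go, so at least 99 must follow another No-Go.
- Reversing the arrows changes nothing, because Go is one-third in both blocks.

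**Ratio that the strict rule needs.** 150 − g ≤ g + 1 gives g ≥ 74.5, so at least 75 Go trials per block.

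**One-third as an independent probability per trial instead of an exact count.** The chance that a block reaches 75 or more Go trials is P(X ≥ 75) for X ~ Binomial(150, 1/3), about 1.8 × 10⁻⁵. Reaching 75 is necessary for the rule but not sufficient.

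**Loose reading: a cap k on the length of a No-Go run, Go kept at one-third.**
- k = 2: the 51 gaps hold at most 51 × 2 = 102 No-Go, and 100 are needed. Every gap is full except for a total shortfall of two. The number of orders is C(51,2) + 51 = 1,275 + 51 = 1,326, all nearly the same pattern of two No-Go and then a Go, so the next stimulus is largely predictable.
- k = 3: the gaps hold up to 51 × 3 = 153, and about 3.2 × 10²⁷ orders are available. This is workable, but the article does not state such a cap.

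**Ratio reversed: Go 2/3, No-Go 1/3.** Per block there are 100 Go and 50 No-Go, with 100 + 1 = 101 gaps for 50 No-Go. The strict rule can be met in C(101,50), about 2.0 × 10²⁹, ways. No-Go trials per assessment become 2 × 50 = 100 instead of 200.

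**The case against.** The best defence is that the ordering phrase was never meant to forbid every pair of adjacent No-Go trials, only long runs. A rare Go is then feasible with a cap of three. This is a possible reading, but the article states no cap, and the tightest feasible one (two) makes the order almost fixed. The sentence needs correction under either reading.

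A reader might infer that the two probabilities were simply swapped. The rule does suit a design in which No-Go is rare, but the documents do not establish this. The rule may have been meant for Go stimuli: 50 Go fit easily into the 101 gaps around 100 No-Go. The article also labels Go the target, which is compatible with a deliberately rare target. Only the authors can say which was intended.

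A reader might also infer that false alarms will sit at floor and that the secondary outcomes cannot answer the objective. The article gives no false-alarm rate, either rested or after 36 hours awake, so the size of any such effect cannot be computed. WCST, Digit Span, ESS and FS-14 do not depend on the task. Hit rate and reaction time remain measurable. The Background links P3 to stimulus evaluation as well as to inhibition. No group is described as receiving a different version of the task, so the ratio does not in itself bias the comparison between groups.

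None of these objections removes the contradiction between ratio and rule.

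**Conclusion.** The contradiction stands. As naturally read, the sequence rule cannot be met at the stated ratio: at least 49 of the 100 No-Go trials in each block must break it. This is pure counting from the article's own figures. It assumes only that the ratio applies within each block, and it also holds over the whole task. Under the looser reading, the fault is a missing run limit.

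This matters more than a wording slip because the sentence defines what subjects do in the task that carries the inhibition-control aim. That a rare Go weakens the task as a measure of inhibition is a design judgement from the stated aim, not a computed effect. The MoCA primary outcome, the sample size built on it, and the secondary outcomes taken outside the task are unaffected.

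**What to change.** Before the first subject, state one Go/No-Go ratio and one sequence rule that can both be met, and check the stimulus script against them.

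- **Preferred, given the stated aim:** Go two-thirds (100 per block) and No-Go one-third (50 per block), with no two No-Go in succession. This makes responding the dominant tendency and keeps 300 trials and the same duration. The downside is that No-Go trials available for ERP averaging fall from 200 to 100 per assessment, so the authors should confirm that 100 is enough after artefact rejection.
- **If a one-third Go share is deliberate:** replace the rule with an explicit, feasible cap on No-Go runs (three or more). Qualify the reading of No-Go false alarms, N2 and P3 as inhibition measures, because withholding is then the majority response.

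Either way, the change is one line of protocol text and a setting in the stimulus script, plus the loss of No-Go trials under the preferred option.

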**Methods:**

We will recruit 60 healthy subjects. The participants will be randomly divided into a treatment group, a control group, a sham electroacupuncture group and a blank group, at a 1:1:1:1 ratio. The primary outcome will be determined by the change from baseline to 36 h in the MoCA score. The secondary results include the amplitude and latency of ERP N2 and P3, Go-hit rates, Go-RTs, No-Go-FA rates, the WCST, the Digit Span Subtest of the WAIS, the ESS score and FS-14. The 15 healthy subjects will not receive acupuncture treatment and ASD, but will receive EEG records and cognition functions test at the beginning and end of the experiment. Electroacupuncture intervention will be performed for 30 min once every 12 h, a total of three times. ERP measurements and other tests will be performed after baseline and ASD, and the statistician and outcome evaluator will be blinded to treatment allocation.

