	**Study Period**						
	**Enrollment**	**Allocation**	**Post-allocation**				**Close-out**
**Timepoint**	** *−1 w* **	**0**	** *Baseline* **	** *12 h* **	** *24 h* **	** *36 h* **	** *48 h* **

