### Data Analysis

We will use SPSS software version 21.0 (IBM Corp, Armonk, New York, US) to perform data analysis. Demographic and baseline data will be analyzed with standard descriptive statistics. Data will be presented as the mean ± standard deviation (SD). A repeated measure ANOVA is employed to analyze the electroacupuncture effects and the time effects on the behavioral data. The repeated measure ANOVA is also used for the analysis of ERP indices. ANOVAs are performed on the N2 and P3 components of the scalp electrodes in the Go/No-Go task. The accepted level of significance for all analyses will be *P* < 0.05.

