## Discussion

The purpose of this trial is to assess the impact of acupuncture on the management of brain cognition control. It is obvious that cognitive function is impaired after sleep deprivation. We intend to compare the effects of time (baseline and 36-h ASD) and intervention (electroacupuncture, sham electroacupuncture and non-electroacupuncture treatment) on executive brain function using a visual Go/No-Go task with simultaneous EEG recordings. Acupuncture is a non-toxic, economical intervention with minimal adverse effects (32) that has been shown to be effective after the therapy (11).

There are several methodological limitations to this study: (1) Due to the characteristics of acupuncture is the non-blinding of the acupuncturist. (2) Only young male subjects will be included; so, the findings may not be generalizable to women and older people. (3) The sample size is small. Despite these limitations, we will use rigorous methodology in this study, and we hope that the trial will help provide new insights into the value of acupuncture and evidence of ERP in executive brain function.

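### Baseline outcomes, including the primary MoCA, are scheduled after allocation; separately, the Go/No-Go task has two candidate baselines 12 hours apart on the clock

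*Protocol article*

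**What the plan says.** **Order of allocation and baseline.** The abstract defines the primary outcome: "The primary outcome will be determined by the change from baseline to 36 h in the MoCA score". In Table 1 the columns run from Enrollment (one week before) to Allocation (time 0), and then Baseline, 12 h, 24 h and 36 h under the label "Post-allocation". MoCA, WCST, digit span, ESS, FS-14 and the EEG record are each marked twice, under Baseline and under 36 h. None of them is marked before Allocation. The items that do come earlier are the handedness questionnaire, sleep log, SCL-90, PSQI and an entry for baseline assessment with no stated content.

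**Who can know their arm.** The Study Setting section calls the trial participant-blinded. The Control Group section gives that arm sleep deprivation without needling, and the Blank Group section gives no intervention and normal hours. The Blinding section covers outcome assessors and data analysts.

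**Go/No-Go sessions.** The Visual Go/No-Go Task Design section states "The participants will arrive at the lab at 20:00 p.m. and perform a Go/No-Go task as a baseline". After a monitored night of sleep, "the experiment will begin at 8:00 a.m. the next morning, taking the Go/No-Go task as 0 h". Then: "After 36 h, the participants will be asked to complete the Go/No-Go task again".

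**Analysis.** The Data Analysis section says "A repeated measure ANOVA is employed to analyze the electroacupuncture effects and the time effects on the behavioral data" and uses the same method for the ERP indices. The Discussion names two time levels: "We intend to compare the effects of time (baseline and 36-h ASD) and intervention".

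**The concern.** There are two separate issues.

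First, a baseline is protected from the effect of assignment only if it is measured before assignment is known. A participant who has learned that he is in the untreated or blank arm may try less hard on a cognitive test, or rate his sleepiness and fatigue differently. A change score subtracts that baseline, so an arm-specific shift goes straight into the group comparison. The primary outcome has this form, and ESS and FS-14 are self-rated.

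Second, the Go/No-Go text offers two pre-deprivation sessions for an analysis with one baseline level, and does not say which is used. The two sessions fall at different times of day and only one matches the 36-h test. The choice decides whether the time effect reflects sleep deprivation alone or sleep deprivation plus a change of clock time. That effect is one of the things the trial sets out to measure.

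**Working it through.** The plan gives no figure of its own for either issue, so there is none to reproduce.

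**1. Clock times.** Inputs are from the Visual Go/No-Go Task Design section.

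- 36-h test: 08:00 + 36 h = 20:00 on the following day.
- From the 20:00 session to the 36-h test: 12 h + 36 h = 48 h. This is two full days, so the clock offset is 0 h.
- From the 08:00 session to the 36-h test: 36 h = 24 h + 12 h. The clock offset is 12 h.

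Only the evening session is matched in clock time.

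**2. A time-of-day shift common to all arms.** The document gives no Go/No-Go values, so the pre-test MoCA means in the Sample Size section serve as an illustration: treatment 26.70, control 25.72, blank 27.32. Assume both deprived arms start at 27.32, and that testing at the other clock time raises the baseline by *d* in every arm. Mean change = follow-up mean − (27.32 + *d*).

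| Assumed *d* | Treatment change | Control change | Difference |
|---|---|---|---|
| 0 | 26.70 − 27.32 = −0.62 | 25.72 − 27.32 = −1.60 | 0.98 |
| 0.5 | −1.12 | −2.10 | 0.98 |
| 1.0 | −1.62 | −2.60 | 0.98 |

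The within-arm change moves by *d*. The between-arm difference does not move, provided the arms are tested at the same times.

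**3. A baseline shift in one arm only.** Let the baseline move by *g* in one arm, with no matching shift at 36 h. The difference in mean change then moves by *g* in absolute size. The yardstick is the pre-test treatment–control difference, 26.70 − 25.72 = 0.98.

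| Assumed *g* | Movement of the difference in change | Share of 0.98 |
|---|---|---|
| 0.25 | 0.25 | 0.25 / 0.98 = 26% |
| 0.5 | 0.50 | 0.5 / 0.98 = 51% |
| 1.0 | 1.00 | 1.0 / 0.98 = 102% |

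The direction depends on the arm and sign. If controls score low at baseline, their decline looks smaller and the difference shrinks to 0.98 − *g*. If they score high, it grows to 0.98 + *g*. Adjusting for baseline would reduce the movement without removing it: with an assumed baseline-to-follow-up correlation of 0.5 and equal SDs, it would be 0.5 × *g*.

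**4. How many participants are exposed.** At 1:1:1:1, 60 / 4 = 15 per arm is expected. Control plus blank is about 30. The blank arm is a non-deprived reference, so about 15 controls bear on the electroacupuncture comparison.

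**The case against.** - **Disclosure before baseline is not stated.** No passage says that participants learn their arm before the baseline tests. Envelopes are opaque and sealed, separate staff handle sequence, recruitment and intervention, and assessors are blinded. This stands as a limit: the bias is possible, not shown. It does not clear the schedule, because Table 1 places allocation first, nothing withholds the result until testing is done, and assessor blinding does not protect self-ratings or effort.
- **The sham comparison is less exposed.** Both the electroacupuncture and sham arms are needled, so knowledge of arm is chiefly a problem for the comparison with control. This stands.
- **A reader might infer that the primary MoCA also has two baselines.** The document does not support that. The two sessions are described for the Go/No-Go task, whose behavioural and ERP measures are secondary. MoCA has one Baseline column with no clock time; the 12-hourly spacing of Table 1 would fit an 08:00 start, but that is inference.
- **A reader might infer that time of day biases the treatment comparison.** It largely cancels when arms share test times. The remaining gap is that clock times for the blank group are not given.
- **Only the 20:00 session is called a baseline.** The 08:00 wording might merely start the clock, and Figure 1, not available for this check, may settle it. The plain reading of the sentence is still a second task.
- **The 08:00 session has a merit of its own.** It follows the monitored night of sleep; the 20:00 session follows an uncontrolled day. This is a real trade-off.
- **A reader might infer that sleep or training failures become losses after randomisation.** The Dropout Criteria name neither, and the timing of the training relative to allocation is not given.

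**Conclusion.** The point holds in two limited parts, and both are worth correcting.

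**Allocation before baseline.** As scheduled, the primary change score and the listed secondary outcomes rest on baselines taken after assignment. About 30 of 60 participants could know their arm by then, about 15 of them in the control arm. Any arm-specific shift at baseline that is not repeated at 36 h passes one for one into the change-score difference: 26% to 102% of 0.98 for assumed shifts of 0.25 to 1.0 point. Those shifts are illustrations. The 0.98 is a difference in pre-test average scores, which the Sample Size section does not describe as changes, so it serves only for scale. The document supports exposure to bias, not its presence or size.

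**Go/No-Go baseline.** For the secondary behavioural and ERP outcomes, the analysed baseline is not identified. If it is the 08:00 task, the within-person time effect carries a 12-hour clock difference. The treatment contrast is largely unaffected if all arms are tested at the same times.

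**What to change.** 1. Complete all baseline outcome tests (MoCA, WCST, digit span, ESS, FS-14, EEG with Go/No-Go) before the envelope is opened, and move Allocation after Baseline in Table 1.
2. Name one Go/No-Go session as the analysed baseline. The existing 20:00 session matches the 36-h test in clock time. Its small downside is that it precedes the monitored night of sleep, so the 08:00 task can be kept as a supporting check of the rested state.
3. State the clock time of the baseline and 36-h sessions, for MoCA as well, and use the same times in all four arms, including the blank group.

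The cost is a change of sequence, a table edit and a few words in the task section. Participants would learn their arm later, and those later assigned to the blank group would have to attend the same baseline session as everyone else. No extra participants or measurements are needed.

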**Figure 1 F1:**
[figure not shown]
Study protocol. In the study protocol, subjects will undergo 36 h periods of acute sleep deprivation (ASD). The black arrows indicate the time points of Electro- encephalogram (EEG) recordings and treatment group receive electroacupuncture treatment.

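### The protocol gives the electroacupuncture interval as 12 h in two places and 11 h in a third, which leaves the gap between the last session and the 36-h assessment uncertain by 2 to 3 h

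*Protocol article*

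**What the plan says.** Three places in the protocol article give the interval between sessions.

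- Abstract, Methods: "Electroacupuncture intervention will be performed for 30 min once every 12 h, a total of three times".
- Treatment Group: "needle retention for 30 min, with intervention performed every 12 h".
- Visual Go/No-Go Task Design: "during which time they will receive acupuncture every 11 h".

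The last of these sections also sets the clock. Time zero is defined by "the experiment will begin at 8:00 a.m. the next morning, taking the Go/No-Go task as 0 h", followed by "The participants will not be allowed to sleep for the next 36 h", and the task is repeated once that period is over. The abstract ties the primary outcome to the same endpoint: "The primary outcome will be determined by the change from baseline to 36 h in the MoCA score". Table 1 lists MoCA and the EEG record at baseline and at 36 h only, so there is a single assessment after the intervention.

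The readable text gives no clock time for any session. The caption of Figure 1 says "The black arrows indicate the time points of Electro- encephalogram (EEG) recordings and treatment group receive electroacupuncture treatment", so the figure may show them, but it is not available here.

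**The concern.** The interval between sessions is part of the definition of the experimental intervention. It also helps to set how long before the only post-baseline assessment the last session ends, and so how recent the stimulation is when MoCA and the ERP measures are taken. All three statements are complete sentences of current text, and they cannot all be followed.

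The 11-h figure cannot simply be set aside as a slip. It stands in the section that runs the experiment hour by hour, and both intervals can yield the three sessions named in the abstract. Two teams, each following a different section, would deliver different schedules and both could claim to have followed the protocol.

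**Working it through.** There is no stated statistical figure to reproduce; the check is schedule arithmetic.

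**Inputs.** Interval d = 12 h (abstract; Treatment Group) or 11 h (Visual Go/No-Go Task Design). Number of sessions = 3 (abstract). Session length = 0.5 h (abstract; Treatment Group). Assessment at 36 h (abstract; Table 1). First-session time t0: not in the readable text, so two assumptions are tried, t0 = 0 h and t0 = d.

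**Formulas.** Session k starts at t0 + (k − 1) × d. The third session therefore starts at t0 + 2d, and the gap from its end to the assessment is 36 − (t0 + 2d) − 0.5.

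| First session | Interval | Session starts (h) | Gap from end of session 3 to 36 h |
|---|---|---|---|
| At 0 h | 12 h | 0, 12, 24 | 36 − 24 − 0.5 = 11.5 h |
| At 0 h | 11 h | 0, 11, 22 | 36 − 22 − 0.5 = 13.5 h |
| After one interval | 12 h | 12, 24, 36 | 36 − 36 − 0.5 = −0.5 h (session 3 starts at 36 h) |
| After one interval | 11 h | 11, 22, 33 | 36 − 33 − 0.5 = 2.5 h |

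**Effect of the interval alone.** With the first session at 0 h: 13.5 − 11.5 = 2 h. With the first session after one interval: 2.5 − (−0.5) = 3 h.

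**Could the session length explain the difference?** If 12 h is counted from start to start, the time from the end of one session to the start of the next is 12 − 0.5 = 11.5 h. If 11 h is counted from end to start, the start-to-start interval is 11 + 0.5 = 11.5 h. Neither conversion turns one stated figure into the other.

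**Could the gap be the same under both?** Only if the first session were moved later under the 11-h interval to make up the 2 h (2 × 12 − 2 × 11). Nothing in the text says so.

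**The case against.** The strongest reply is that the session times may not be missing at all. Figure 1 is described as marking them, and the intervention rows of Table 1 are empty in the text at hand, which would fit graphical bars lost when the PDF was read. This stands: absence of the session times is not a finding here, and the start times used above are assumptions. It does not remove the contradiction, because a figure with one fixed interval can agree with 12 h or with 11 h but not with both.

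A second reply is that, if one schedule is applied to both needled arms, the comparison of electroacupuncture with sham is not biased. The Placebo Group section says that procedures and other settings match those of the treatment group. This also stands. What suffers is the definition and reproducibility of the intervention, and the meaning of the 36-h result, unless staff follow different sections for different participants.

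Three stronger readings are tempting, and the documents do not support them.

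- A reader might infer that the gap could lie anywhere from none to more than 11 h. Most of that spread comes from varying the unknown first-session time. With a matched start rule, the contradiction itself accounts for 2 to 3 h.
- A reader might infer four sessions, since an 11-h interval from 0 h would allow starts at 0, 11, 22 and 33 h. The abstract fixes the total at three, and the section with the 11-h figure gives no other count.
- A reader might infer that the third session collides with the 36-h tests and reveals allocation to the blinded assessors. That needs the 12/24/36 h schedule, which fits poorly with a text that places acupuncture within the 36 h and the repeat task after it. Even then, sham sessions are set up the same way, so seeing a session would at most separate needled from un-needled arms. Nothing says that assessors attend sessions.

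**Conclusion.** The contradiction is real: 12 h in the abstract and the Treatment Group section, 11 h in the Visual Go/No-Go Task Design section, with no readable text to reconcile them. It is more than a clerical matter, because the figure is an operating instruction that defines the intervention and affects its distance from the only post-baseline MoCA and EEG.

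Its size is a shift of 2 h or 3 h in that gap, depending on the start rule. This rests on three sessions of 30 minutes, equal spacing, and the same start rule under both intervals. The primary endpoint, its 36-h time point and the sample size calculation are not affected. The documents do not show which interval is intended, and this review takes no position on it.

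**What to change.** - Reconcile the abstract, the Treatment Group section and the Visual Go/No-Go Task Design section to one interval and one session count, both chosen by the investigators.
- Check Figure 1 and the intervention rows of Table 1 against that choice.
- State each session time relative to 0 h, and say whether the interval runs from start to start or from end to start.
- State the resulting interval from the end of the last session to the start of the 36-h MoCA and EEG, and say explicitly that it applies equally to the electroacupuncture and sham arms.

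Before the first participant is treated, this costs only protocol wording and no extra resources. If sessions have already been given, the times actually used should be documented and reported with the correction.
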